**Predictor Variables**

Predictor demographic variables will include participant age, gravidity, parity, history of cervical cancer screening, marital status and number of current and previous sexual partners. Clinical predictors will include WHO status of HIV disease, CD4+ count, opportunistic infections, previous sexually transmitted infections and current use of anti-retroviral therapy.

For Specific Aim 2c, predictor variable will be p16^INK4a^ ELISA levels found during initial screening. The other variables above will be collected and treated as potential confounders.

**Outcome variables**

**Specific Aim 1:**

- VIA or VILI result (positive or negative)
- Colposcopy result (absence of CIN2/3) or result of colposcopically-directed biopsy if indicated for suspicion of CIN2/3, as is commonly used reference standard for cervical cancer screening studies.^90, 91^

**Specific Aim 2:**

- p16^INK4a^
- HR-HPV (types: 16, 18, 31, 33, 35, 39, 45, 51, 52, 56, 58, 59, 68)
- Colposcopy result (absence of CIN2/3) or result of colposcopically-directed biopsy if indicated for suspicion of CIN2/3

Specific Aim 2c:

- Colposcopy result (absence of CIN2/3) or result of colposcopically-directed biopsy if indicated for suspicion of CIN2/3

**Specific Aim 3:**

- Presence and quantity of HIV-1 RNA viral load in cervicovaginal secretions at the time of VIA/colposcopy. HIV-1 quantity will be expressed as log copies per microliter (µL) of vaginal fluid.

**Specific Aim 4:**

- Presence and quantity of HIV-1 RNA viral load in cervicovaginal secretions at each of the study time points.

**ETHICAL CONSIDERATIONS**

Human Subjects Involvement and Characteristics

The study described in this proposal will involve a total of around 1,800 HIV-infected women receiving care at the FACES clinics in Kisumu, Kenya. Women will be included in the study for the cross-sectional validation study if they are: 1) 25 years or older 2) not pregnant 3) accept cervical cancer screening 4) have a satisfactory Visual Inspection with Acetic Acid (VIA). Participants will be recruited for the prospective follow-up study (Specific Aim 2c) if they meet the above criteria, and were found to have normal colposcopy or CIN1 upon initial screening with p16^INK4a^ biomarker measurement. Participants will be recruited for the prospective post-LEEP HIV-1 shedding study if they meet the above criteria, have undergone LEEP for treatment of CIN2/3 and agree to remain abstinent for three days prior to each of the follow-up visits. To participate in any of these study activities, women must be willing and able to participate, be able to sign or mark a consent form, and speak one of the languages into which the consent form and data collection instruments have been translated, including English, D’Luo and Kiswahili.

Sources of Materials

Data for this study will be collected from several sources. Clinical and demographic data will be obtained through chart reviews and physical examination. We will also obtain clinical information from the colposcopic examinations. Information from the colposcopy and if performed, biopsy, will be entered into the participants’ medical records as it will be used to direct clinical care. We will also obtain cervical specimens for p16^INK4a^ and HR-HPV testing and vaginal wick specimens for women in the post-LEEP HIV-1 shedding study. These will be obtained solely for research purposes, and will therefore not be entered into the participant’s medical record. All data collection will take place in a private study room.

Potential Risks

We anticipate that the potential risks to participants in the study will be minimal. Study subjects may feel discomfort or embarrassment during the pelvic exam. Participants may be at risk for psychological or emotional discomfort at different stages of the study if they have a diagnosis of CIN2/3 and learn about potential risk of cervical cancer. Participants may risk some discomfort and bleeding after the colposcopy and biopsy, if performed. We anticipate that this will be minimal, as exams will be performed in a very gentle manner by trained clinicians. We do not anticipate physical discomfort from the collection of cervical specimens, however participants in the prospective HIV-1 shedding study may risk some post-LEEP bleeding after the speculum exam at the follow-up study visits. We anticipate that this will be minimal, as speculum exams will be performed in a very gentle manner by trained clinicians and we do not anticipate physical discomfort from the collection of Sno-Strip specimens during the follow-up visits.

Adequacy of Protection Against Risks

To reduce the likelihood of participants experiencing psychological discomfort, we will make every effort to create a secure and trustworthy environment. Study staff that counsel participants and carry out examinations will undergo training on culturally sensitive ways to reduce discomfort and embarrassment during the pelvic exam. To assist participants who may experience psychological discomfort when learning of a diagnosis of cervical dysplasia, we will ensure access to experienced counselors who work at FACES. Participants will be screened for signs of depression or difficulty coping with the added diagnoses at study visits.

All study staff will be thoroughly trained in the study protocol, study procedures, good clinical practices and protection of human subjects prior to starting the study. All exams will be performed gently and in a way that most minimizes discomfort, bleeding or anxiety in the participants.

Recruitment and Informed Consent

Women will be recruited in the cervical cancer screening rooms in the FACES clinics at Lumumba and Kisumu District Hospital. Upon enrollment into care at FACES, all patients take part in an HIV education course, which includes an introduction to cervical cancer risk and opportunities for screening. Health education talks occur daily in the clinic waiting area; among the covered topics are cervical cancer screening. Women who are eligible for cervical cancer screening are counseled in private by a triage nurse prior to their clinical visit. After their clinical visit, women who agree to screening are seen in a private gynecologic examination room. A trained study nurse will take women who meet the eligibility criteria through an informed consent process. As part of the informed consent process, potential participants will be informed of the purpose and methods of the study, procedures to protect the confidentiality of their clinical and study related information, their right to withdraw from the study at any time, the fact that their participation or non-participation will not affect the medical care that they receive at FACES, and persons to contact if they have questions about the study after completion of the study visit. The women will also be asked permission to obtain information from their medical records. Study subjects will be provided with a copy of the entire consent as well as an information sheet in simple language to take home. Participants may provide verbal consent and may place their mark on the consent form, if they are unable to provide a signature. No study procedures or data collection will take place prior to obtaining informed consent.

For Specific Aim 2c, we will prospectively recruit women who participated in p16^INK4a^ ELISA screening in the last one-year and who where found to have a normal colposcopy or CIN1. For the women found to have CIN1 at initial screening, per current protocol they would be due for a repeat colposcopy after one year. These women will be recruited into this follow-up study when they present for their clinically indicated colposcopy visit. For the remainder of eligible women who were found to have normal colposcopy at initial screening, they will be recruited for this follow-up study separately as they present for their routine medical visits. For these women, repeat screening would not be indicated at the one-year follow-up and will be done only for study purposes. We recognize that there will be a potential risk of lost confidentiality because women in this group will be identified based on their previous study participation. We will take measures to ensure the patients’ privacy is protected, such as only using patient ID numbers to flag files of eligible study participants, rather than using patient’s names.

Protection Against Risk

UCSF’s Institutional Review Board, the Committee on Human Research, and KEMRI’s Steering Committee, Scientific Steering Committee and Ethical Review Committee will review this protocol prior to study initiation. I will ensure that all procedures conform to US, Kenyan and international ethical standards regarding research involving human subjects. Guidance from [name], the site-PI at FACES, will be critical in assuring that the protocol meets strict Kenyan standards for protection of research subjects. We will also seek assistance from the FACES Community Advisory Board (CAB) comprised of a diverse group of members of the Kisumu community, including FACES patients. The CAB will meet with members of the research team bimonthly to quarterly throughout the study to ensure that the study team is sensitive to potential sources of risk and discomfort to study subjects.

All participants will be assigned a unique alphanumeric code. One file linking the study identifiers with individual names will be kept by the Principal Investigator in a secured computer file. The file will be destroyed after data analysis is complete. All study forms will be maintained in a locked file cabinet in the FACES clinic.

Potential Benefits of the Proposed Research to the Subjects and Others

The research described in this plan will not provide any direct benefit to the participants, beyond a potential increase in knowledge about cervical cancer screening and prevention gained from spending more time with study staff and study clinicians. According to KEMRI regulations, participants will only be reimbursed for their transportation expenses related to participation in the study. Women enrolled in the cross-sectional/case-control portion of the study will not require an extra study visit, therefore they will be reimbursed with a meal voucher only. Women who provide consent and enroll in the longitudinal study will receive a transportation reimbursement of 300Ksh, in accordance with the level set by KEMRI.

Importance of the Knowledge to be Gained

The research plan described above will provide important information about an effective, resource-appropriate cervical cancer screening and prevention strategy that will help reduce the incidence and mortality from cervical cancer among HIV-infected women. This may have the potential to improve access for women who are at high-risk for the disease both biologically and because they live in settings where they have limited access to care. The information from the post-LEEP HIV-1 shedding study will help inform future research, specifically, a randomized trial to evaluate cervical cancer screening and treatment in resource-limited settings. Additionally, information about the amount and duration of post-LEEP HIV-1 shedding may change the understanding of post-LEEP infectivity and counseling for post-LEEP sexual activity, ultimately affected HIV transmission rates. Together these aims comprise the next step in the effort to accurately diagnose and safely treat cervical dysplasia among HIV-infected women in resource-limited settings.

Privacy and Security of Health Records

All paper and electronic medical records for participants and potential participants in this study will be secured and maintained in compliance with UCSF campus administrative policy 650-16.

**DATA QUALITY AND MANAGEMENT**

Staff Training: Study exams will be carried out by clinical officers and nurses after undergoing training in speculum exam, VIA, specimen collection, colposcopy and directed biopsy. The training will be based on the International Agency for Research on Cancer,^75^ PATH and WHO^74^ curricula and will consist of a series of didactic lectures, discussions, review of cervical photographs and hands-on experience. All study staff will undergo training in Good Clinical Practices, informed consent, participant confidentiality and study-specific procedures. After satisfactory completion of training, including an examination and proctored procedures, staff will receive certification. Periodic training and assessment sessions will be done throughout the study. Lab technicians will be oriented in the proper handling, storage and transport of laboratory specimens.

Quality Assurance: The main study measurements which will be subjected to quality assurance measures to eliminate the risk of random error and measurement bias: VIA and colposcopy reading, interpretation of histopathology specimens, p16^INK4a^ levels, HR-HPV reading and measurement of HIV-1 viral load. The quality of VIA and colposcopy is dependent on the training, supervision and periodic assessment of the clinical officers performing the examinations. To further reduce random error, all colposcopies will be interpreted using the guidelines of the IFCPC as has been done in prior studies.^89^ Histopathology specimens will be read by a trained cytopathologist at KEMRI. The first 20% of specimens will be double read by a pathologist at UCSF, who will be blinded to the results of the KEMRI pathologist. Discrepancies will be clarified by consultation and review of the specimens by both pathologists. If no consensus if reached, the results will be reviewed by a third, blinded UCSF pathologist.

The main outcome for this specific aim will be p16^INK4a^ values. Monoclonal antibody testing for p16^INK4a^ will be performed on all specimens using an ELISA-based biochemical assay currently available only in specified research laboratories. Samples for the p16^INK4a^ ELISA will be transferred into a collection vial with a prototypic sample lysis medium (MTM Laboratories, Heidelberg, Germany) containing nonionic detergents (<1%). Lysed samples will be stored frozen until the ELISA-based measurement of p16^INK4a^ protein concentration is performed. Next, 100-µL aliquots of each individual sample were subjected in duplicate to a prototypic colorimetric sandwich-ELISA protocol (MTM Laboratories), which is based on two different p16^INK4a^-specific monoclonal antibodies, an antibody that was coated to the solid phase of a microtiter plate (clone E6H4) and an antibody that was conjugated to horseradish peroxidase for the detection of captured p16^INK4a^ protein (clone D7D7). For quantification, calibration curves will be established by using reagent standards that contained known concentrations of p16^INK4a^ antigen. p16^INK4a^ protein concentrations in the clinical samples were calculated as arbitrary units (U/mL) based on the standard curve. Average values of double measurements were used, and the coefficient of variation was <15% at a cutoff value of 16 U/mL. In order to ensure the reliability of the biochemical assay measurements, quantitative levels of p16^INK4a^ will be compared with levels found in immunohistochemical (IHC) staining of the corresponding biopsy specimens. Correlation will be determined through the calculation of a Kappa coefficient, which we seek to be greater than 0.8. In cases of normal colposcopy (and hence no biopsy), p16^INK4a^ IHC values will be assigned as zero. The IHC staining will be done by pathologists at KEMRI, who have experience in this technique and will undergo further study-specific training coordinated by [name] [name] at the German Cancer Research Center in Heidelberg.

HR-HPV DNA testing will be done at the MTM laboratories, under Dr. [name]’s direction. Testing will be done using fluid from the same collection vial as the p16 testing, and will be done using the Hybrid Capture 2 (Qiagen, Inc.) nucleic acid amplification test for 13 high risk HPV types 16, 18, 31, 33, 35, 39, 45, 51, 52, 56, 58, 59, 68. Results of the HPV DNA assay will be expressed as a ration of relative light units (rlu ratio) to the average of three positive controls, with 1.00 as the cut-off for test positivity. Internal quality assurance parameters and positivity cut-off parameters are determined by the manufacturer’s instructions. Positive HC2 tests will then be typed using reverse dot blot hybridization with recombinant HPV type-specific plasmids (Luminex, Inc). If the confirmatory test is negative, the amplimers will be cloned and sequenced. Only Hybrid Capture 2-positive samples confirmed by reverse dot blot hybridization or sequencing will be classified as HPV-positive.

The ARI-UCSF Laboratory of Clinical Virology, which will perform the HIV-1 RNA testing on genital specimens, is licensed by the State of California for clinical virologic and immunologic testing (CLIA # 05D0969871). The laboratory adheres to a comprehensive Quality Assurance program, and undergoes regular monitor visits from Laboratory Field Services and PPD, a contractor for the NIH/DAIDS, to ensure adherence to Good Clinical Laboratory Practices (GCLP) while supporting federally funded clinical trials.

Permits will be obtained through KEMRI prior to shipping specimens to UCSF and the MTM laboratories. We will continue to search for and work with local partners with laboratory capacity and expertise to run specimens for genital HIV-1 RNA. When genital HIV-1 RNA testing has been validated in local laboratories, we will run our specimens through those labs. We anticipate that this will be more efficient, less expensive and help to build local capacity. The p16^INK4a^ biochemical assays are not available at this time in Kenya, one of the reasons we are carrying out the work here. We are confident that the experience and results from this project will lead to further p16^INK4a^ testing and development of a point-of-care assay, work to be carried our by laboratories and clinical researchers within Kenya in the future.

Data Storage: The study will be conducted within the existing clinic settings in the Nyanza Province. Data will be collected from the electronic medical record and on study-specific forms (Appendices F and G). Study data will be included as part of the patient’s medical file and maintained in locked file cabinets within the clinic. Data will be abstracted to computers by data entry clerks and managed by the assigned data manager at each site. Abstracted data will be labeled by unique study ID only. A file correlating study ID and medical file number will be kept in separate password-protected Excel computer file and accessible only to the core research team. Additionally, all study computers are password protected and kept in locked offices within the clinics.

Statistical Analysis:

Statistical analysis for all specific aims will be carried out using STATA and SPSS software.

**Specific Aim 1**: The goal of specific aim 1 is to calculate the sensitivity, specificity and predictive values of VIA and VILI for CIN2/3, with colposcopy as the gold standard. Colposcopy will be performed on every participant, regardless of screening result, to avoid verification bias.^92^ To calculate the sample size for this study, we assume that the prevalence of CIN2/3 among HIV-infected women at FACES will be 7%, as has been seen in the cervical cancer screening program at FACES.^78^ Sample size calculations will be based on prior estimates of VIA sensitivity, as these are more prevalent and therefore have more precision.

Sensitivity: Previous studies have shown that VIA has a sensitivity of 60-86%^39, 40, 91, 93-97^ for detection of CIN2/3 among healthy women, which is comparable to the sensitivity of cervical cytology and would be an acceptable test characteristic for this setting. In order to determine sensitivity, we will construct a 2 x 2 table, and divide the number of women with a true positive VIA result (i.e. those with disease diagnosed by colposcopy and VIA) by the number of true positive VIAs plus the number of false negative VIAs. Specificity: Specificity values for VIA range from 64 to 94% for the detection of CIN2/3.^39, 40, 91, 98, 99^ To determine specificity of VIA, we will divide the number of participants with true negative VIA (i.e. has no disease diagnosed colposcopically) by the number of true negative tests plus the number of false positive tests.

In addition to sensitivity and specificity, we will calculate the positive and negative predictive values of VIA. Studies have shown a PPV of VIA for CIN2/3 to range from 9-27% in HIV-negative women.^97, 100, 101^ To calculate the PPV in our study, we will divide the number of participants with a positive VIA by the number of participants found to have CIN2/3 on biopsy. VIA has been shown to have a negative predictive value (NPV) of 91-99.5% in HIV-negative women.^102^ To calculate the NPV, we will divide the number of participants with a negative VIA by the number of participants with no evidence of disease at colposcopy, either by visual impression or a negative biopsy result. Confidence limits for estimates of sensitivity, specificity, PPV and NPV will be exact, based on the binomial distribution.

Finally, we will compare the test characteristics between the two screening modalities using a McNemar’s test of proportions.

**Specific Aim 2**: To determine the cut-off value for the p16^INK4a^ biochemical assay that will provide the highest sensitivity and specificity for the detection of CIN2/3, we will construct a Receiver Operating Characteristic (ROC) curves using the results of the ELISA-based assay and the histology specimens. An ROC curve will allow us to plot the True Positive Rate (TPR) and the False Positive Rate (FPR) for various values of the p16^INK4a^ assay. As TPR is equivalent to the sensitivity of a test, and 1-FPR is the specificity, the graphical representation, as well as the calculated Area Under the Curve will allow us to determine the cut-off value for p16^INK4a^ to define a “positive test” with the highest sensitivity and specificity.

We will compare the absolute differences in sensitivity and specificity for detection of CIN2/3 of p16^INK4a^ and HR-HPV using the Mann-Whitney U test. The values of p16^INK4a^ will be determined from the ROC curves in Specific Aim 2. The sensitivity and specificity of the HR-HPV tests will be calculated as below:

- To calculate **sensitivity**, we will divide the number of women with a true positive test by the number of true positives plus the number of false negative HR-HPV testing.
- To calculate **specificity**, we will divide the number of participants with no disease diagnosed colposcopically (true negatives) by the number of true negative plus false positive HR-HPV tests.

Confidence limits for estimates of sensitivity and specificity will be exact, based on the binomial distribution.

**Specific Aims 2c:** To compare the rate of detecting CIN2/3 at one-year follow-up between women with normal or increased levels of p16^INK4a^ at baseline, we will use the Pearson’s chi-square test to investigate any significant differences in the proportions. Based on our sample size calculations, we aim to have 80 percent power with a two-sided alpha of 0.05. To compare the rates of developing CIN2/3 at one-year follow-up between women with persistently elevated p16^INK4a^ compared to those with only one elevated measurement, we will also use the Pearson’s chi-square test to look for statistically significant differences in proportions of CIN2/3 in the two groups.

**Specific Aim 3:** To compare the presence and magnitude of HIV-1 genital shedding between women with and without cervical dysplasia we will compute the odds ratio of HIV-1 detection in genital secretions with 95% confidence intervals. Multivariate analyses will be performed using logistic regression to control for demographic and clinical confounders. Potential confounders include WHO stage of HIV disease, CD4+ count, plasma HIV-1 viral load, opportunistic infections, previous STIs and current use of anti-retroviral therapy.

**Specific Aim 4:** The goal of specific aim 4 is to determine the magnitude and duration of increased HIV-1 genital shedding that occurs after treatment with LEEP. Observed time trends in log copies of genital HIV-1 RNA will initially be evaluated via exploratory analyses of longitudinal measures based on scatter plot smoothing methods. Results will allow us to assess possible nonlinearities in trends, as well as investigate differences in results between subgroups of interest. The subgroups we are looking at include participants on HAART and who have CD4+ counts below 200. Further analyses will focus on estimation of post-LEEP changes from baseline levels in log copies of HIV-1 RNA using linear mixed effects regression methods. The primary predictor will be time on study (measured in weeks post-treatment). Initial models will include separate coefficients for each week of observation post-treatment (2, 4, 6, 10 and 14). Hypothesis 2 will be addressed directly via tests constructed about these coefficients. We will also explore the effect on results of adjustment for selected covariates, including demographic characteristics and baseline descriptors of participant health status.

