**Specific Aim 2:** We based our sample size calculations for this aim on the following calculations: a sample of 42 women with positive results and 60 with negative results will achieve 90% power to detect a difference of 0.1 between the histology result and the AUC for the p16^INK4a^ assay using a two-sided z-test at a significance level of 0.05.^84^ Histology is the gold standard for diagnosis of CIN, which would give it an AUC of 1.0; a 0.1 difference mean an AUC for p16^INK4a^ of 0.90, which would make it an excellent diagnostic tool. Our power to detect even greater difference with this sample size would be even greater. We will enroll ***60* women with negative colposcopies, and *140* women with positive colposcopic exams**. The positive predictive value of a positive colposcopy at FACES is approximately 57% for CIN2/3 and 89% of any diagnosis of CIN.^85^ A sample of 140 women with positive colposcopic exams will ensure that we have an adequate number of women with the positive result of interest (CIN2/3) to achieve our specific aim, and potentially enough women with lower levels of CIN to obtain preliminary information regarding test characteristic among this group. In order to calculate the specificity and sensitivity (SA 2b), we will use the sample sizes calculated above for specific aim 1.

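### The p16 reliability check calls kappa a correlation between an ELISA concentration and an IHC staining level; kappa needs shared categories, none are tied to it, and the 0.8 goal then depends partly on the cut-offs chosen

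*Protocol*

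**What the plan says.** The check is in the Protocol, Data Quality and Management, Quality Assurance. To show that the biochemical assay is reliable, "quantitative levels of p16^INK4a^ will be compared with levels found in immunohistochemical (IHC) staining of the corresponding biopsy specimens". The ELISA result is continuous: "protein concentrations in the clinical samples were calculated as arbitrary units (U/mL) based on the standard curve". The statistic and its goal follow: "Correlation will be determined through the calculation of a Kappa coefficient, which we seek to be greater than 0.8". For women with a normal colposcopy and so no biopsy, "IHC values will be assigned as zero".

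Two ELISA cut-offs appear in the Protocol, neither attached to the kappa:

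- In the same paragraph, as part of the assay's precision: "the coefficient of variation was <15% at a cutoff value of 16 U/mL".
- Under Statistical Analysis, Specific Aim 2, where the ROC curve is built against histology and "the calculated Area Under the Curve will allow us to determine the cut-off value for" the assay. Aim 2b under Objectives also uses the ROC cut-off.

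For IHC, the paragraph gives no score, no positivity threshold and no weights. The Background mentions a published scoring system for p16-positive cells, but the plan does not adopt it for this check.

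**The concern.** The statistic named does not fit the comparison named. Two quantitative or graded measurements on different scales call for a measure of association. Kappa instead asks whether two raters put the same woman in the same category, and a concentration in arbitrary units has no categories in common with a staining level.

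To obtain a kappa, the analyst must first cut both measures, which changes the question from whether the levels move together to whether two yes/no labels coincide. The answer then depends on where each cut is placed. A low kappa could mean that the assay tracks tissue p16 poorly, or only that one threshold is more lenient than the other, and the single number would not say which. This is the Protocol's only check of the ELISA against tissue p16, so its result should be readable.

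**Working it through.** **Nothing to reproduce.** The 0.8 is a goal. No sample size, cut-off, category or weight comes with it.

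**Raw values.** Two lists on different scales share essentially no identical values, so observed and chance agreement are both near 0, and so is kappa, however strong the association. No analyst would run this; it only shows that categories must be supplied.

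**After dichotomising.** Let p1 and p2 be the ELISA-positive and IHC-positive fractions. If the assay ranks women exactly as IHC does, one positive group lies inside the other and the only discordance is |p1 − p2|:

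- po = 1 − |p1 − p2|
- pe = p1·p2 + (1 − p1)(1 − p2)
- maximum kappa = (po − pe)/(1 − pe)

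The fractions below are assumptions.

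| p1, p2 | po | pe | maximum kappa |
|---|---|---|---|
| 0.50, 0.50 | 1.00 | 0.50 | 1.00 |
| 0.50, 0.40 | 0.90 | 0.50 | 0.40/0.50 = 0.80 |
| 0.60, 0.40 | 0.80 | 0.48 | 0.32/0.52 = 0.62 |

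The goal is a value above 0.8, so the second row does not meet it either.

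**With the Protocol's own counts.** The sample size section for Specific Aim 2 plans 140 women with a positive colposcopy and puts the yield at 57% for CIN2/3 and 89% for any CIN: 0.57 × 140 = 79.8 (about 80) and 0.89 × 140 = 124.6 (about 125). The Background says that CIN1 rarely stains positive, so I assume 80 IHC-positive, with 125 as the other end of the range. For a perfectly ranked assay in the 140 biopsied women:

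| ELISA-positive | kappa if IHC-positive = 80 | kappa if IHC-positive = 125 |
|---|---|---|
| 65 | 0.79 | 0.19 |
| 80 | 1.00 | 0.28 |
| 95 | 0.77 | 0.40 |
| 110 | 0.53 | 0.61 |
| 120 | 0.36 | 0.84 |
| 125 | 0.28 | 1.00 |

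With 80 IHC-positive, kappa exceeds 0.8 only when 66 to 93 women are ELISA-positive.

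A count of 110 is plausible. The sample size text for Aim 2c says that roughly half of the pilot women with normal colposcopy or CIN1 had raised p16. Applying that share to the 60 biopsied women without CIN2/3 (assumption), and counting all 80 with CIN2/3 as positive, gives 80 + 30 = 110. Then po = (80 + 30)/140 = 0.786, pe = (80 × 110 + 60 × 30)/140² = 0.541, and kappa = 0.245/0.459 = 0.53.

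**Why the word correlation matters.** The two scales differ. For a bivariate normal pair cut at both medians (assumption), kappa = (2/π)·arcsin(ρ). A correlation of 0.90 gives 0.71, and a kappa of 0.80 needs ρ = sin(0.8 × π/2) = 0.951. A goal of 0.8 therefore means different things for the two statistics.

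All counts here use biopsied women only, so the problem is separate from the zero assigned to women without a biopsy.

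**The case against.** The strongest reply is that the natural reading is a 2×2 table. An ELISA cut-off of 16 U/mL stands in the same paragraph, an ROC cut-off is planned, and the Background describes IHC as staining positively or not. Nothing requires kappa to be computed before the ROC cut-off is known. Naming the thresholds could be left to an analysis plan or laboratory manual. For a test meant to end as a yes/no result, disagreement between labels at the working cut-offs is a real property that kappa is meant to detect.

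Much of this stands. A reader might infer that the criterion cannot be computed at all. The documents do not support that, because usable ELISA cut-offs exist, although none is linked to the check. A reader might also infer that a sound assay will fail. It need not: with matched counts kappa is 1.0, and under the 80-positive assumption the passing range of 66 to 93 is wide. Nor is a kappa of 0.71 at ρ = 0.90 a false failure, since that is not perfect agreement.

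The reply does not repair the mismatch. The Protocol compares quantitative levels and calls the result a correlation, and that is a choice of statistic made in the text rather than a detail deferred. The two available ELISA cut-offs are not calibrated to IHC: one comes from a precision statement and the other from histology.

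**Conclusion.** The point holds at moderate weight. The statistic does not match the stated comparison, and no category on either side is tied to it. After dichotomising, a perfectly ranked assay is capped at 0.80 (50% v 40% positive) or 0.62 (60% v 40%), and reaches 0.53 in the scenario built from the Protocol's counts. The positive fractions, the IHC-positive counts and the use of the pilot share are assumptions. The dependence of kappa on the match between the two fractions does not rest on them.

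A reader might infer that a kappa below 0.8 would undermine the results of Aims 2 to 2c. The documents do not support this. The value is something sought, no action follows from missing it, and no analysis for those aims uses it: the ROC analysis runs against histology and the Aim 2c tests against CIN2/3. The Protocol also describes calibration curves, duplicate measurements and a coefficient of variation for the assay. What is at stake is whether the quality-assurance result can be interpreted.

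**What to change.** In Quality Assurance, replace the kappa sentence as follows:

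1. In women with an observed biopsy, assess the quantitative comparison by the Spearman rank correlation, with a 95% CI, between ELISA U/mL and a graded IHC score, and name that score.
2. If a yes/no comparison is also wanted, name one ELISA cut-off and one IHC positivity threshold. Report positive and negative percent agreement there, with kappa as a supplement, and call it agreement.

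Do not carry 0.8 over to the rank correlation unexamined. A graded score has ties: in a simulated, perfectly monotone example with 200 women and a four-level score (120, 30, 25 and 25 women per level), Spearman was 0.88. If IHC is recorded only as positive or negative, item 2 is the main comparison.

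Do not move the 0.8 goal to an intraclass correlation of the duplicate ELISA wells. That measures repeatability, which the duplicates and coefficient of variation already address, and would leave the comparison with tissue without an assessment.

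The cost is a few lines of Protocol text and analysis code. No new assays or specimens are needed.
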